### Data management

A comprehensive database will be created to monitor each participant’s progress and record all assessment data. All collected information will be securely stored on password-protected computers accessible only to the researchers directly involved in the study. An independent investigator will oversee the progress and safety of data collection. Data analysis will be conducted once recruitment and data collection have been completed.

### Statistical analysis

Statistical analysis will be performed with Statistical Package for the Social Sciences version 29.0 (SPSS Inc, Chicago, IL). The significance level will be 0.05 for all statistical analyses. Descriptive statistics will summarize participants’ baseline characteristics and study outcomes. Categorical variables will be presented as absolute and relative frequencies (n, %), whereas continuous variables will be expressed as mean ± standard deviation or, when appropriate, as median and interquartile range, together with 95% confidence intervals. The Shapiro–Wilk test will assess the normality of continuous variables. To ensure comparability between groups at baseline, appropriate parametric or nonparametric tests will be applied depending on data distribution: t-tests or Mann–Whitney U tests for continuous data, and Chi-square tests for categorical data.

To examine the effects of the intervention across time, linear mixed-effects models will be employed to analyze group‑by‑time interactions across the three measurement points. Significant main or interaction effects will be further explored through Bonferroni-adjusted post hoc comparisons. In cases where data deviate from normality, within-group changes will be analyzed using the Friedman test, followed by Wilcoxon signed-rank tests for pairwise comparisons. Bonferroni correction will be applied to control for multiple testing and Type I error.

Between-group differences at each time point will be examined using independent-samples t-tests (accompanied by Levene’s test for homogeneity of variances) for normally distributed data, or Mann–Whitney U tests for non-parametric data. Categorical outcomes will be compared using Chi-square or Fisher’s exact test, as appropriate.

All analyses will follow the intention-to-treat (ITT) principle, including every randomized participant in the group to which they were initially assigned, regardless of adherence, or protocol deviations. Missing data will be managed through suitable statistical procedures, such as last observation carried forward (LOCF) or multiple imputation, depending on the type and extent of missingness.

Effect sizes will be computed to determine the magnitude of observed differences, using Cohen’s d for parametric tests and effect size r for non-parametric analyses, both within and between groups for the primary outcomes. Effect sizes will be reported with 95% confidence intervals, and interpretation will consider both statistical significance and clinical relevance, using established Minimal Clinically Important Differences (MCIDs) for all outcomes. Insignificant, small, medium, and large differences will be reflected in effect sizes of < 0.2, 0.2–0.5, 0.5–0.8, and > 0.8, respectively [54].

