### Sample size calculation

Sample size estimation was performed using G*Power software (version 3.1.9.7), taking the primary outcome variable, balance, assessed by the Mini-BESTest scale as the reference. Although the hypothesis anticipates superior outcomes for the experimental IVR intervention compared to the control condition, a two-tailed alternative hypothesis was adopted to maintain a conservative statistical approach. The calculation was based on a repeated measures design involving two groups and three time points, but specifically on the expected difference between groups at the post-intervention time point assuming a moderate effect size (d = 0.71), a significance level of 0.05, and a statistical power of 80%**.** Although the study includes follow-up measurements, this approach provides a conservative estimate expected to offer adequate power for comparisons at follow-up. Because the sample size calculation relies on the expected between‑group difference at the post‑intervention time point, assumptions about the correlation between repeated measurements will not be necessary. Under these conditions, the required sample size was determined to be 50 participants, with 25 allocated to each group. To accommodate an estimated 10% attrition rate, the final target sample was increased to 56 participants (28 per group).

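### Baseline significance tests cannot establish that the arms are comparable, and the visit-wise between-group tests carry no baseline term; adjust those contrasts for baseline instead

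*Protocol article*

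**What the plan says.** The relevant text is in three sections of the protocol article.

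- **Baseline (Statistical analysis).** "To ensure comparability between groups at baseline, appropriate parametric or nonparametric tests will be applied depending on data distribution". The tests named are "t-tests or Mann–Whitney U tests for continuous data, and Chi-square tests for categorical data", and "The significance level will be 0.05 for all statistical analyses". No margin, standardised difference or other criterion for comparability is given. Baseline characteristics are also to be summarised descriptively.
- **Outcomes (Statistical analysis).** A linear mixed model examines the group-by-time interaction over three measurement points. Separately, "Between-group differences at each time point will be examined using independent-samples t-tests", with Mann–Whitney tests for non-normal data. No baseline covariate is named for these visit-wise tests. When data are not normal, changes over time are analysed within each group by Friedman and Wilcoxon tests.
- **Size (Sample size calculation).** The calculation targets the between-group difference after the intervention, with d = 0.71, alpha 0.05 and 80% power, and "a two-tailed alternative hypothesis was adopted to maintain a conservative statistical approach". The result is that "the required sample size was determined to be 50 participants, with 25 allocated to each group", raised to 56 (28 per group) for 10% attrition.

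Under Allocation and blinding, participants are randomised 1:1 after the baseline evaluations.

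**The concern.** A significance test asks whether a difference could have arisen by chance. After randomisation the answer for baseline variables is already known, so the p-value says nothing useful about balance. The practical question is whether the imbalance that did occur is large enough to affect the treatment comparison. That depends on its size and on how strongly the variable predicts the outcome, not on whether p falls below 0.05.

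This matters because the contrast used to size the trial is an unadjusted comparison of the arms at the post-intervention visit. A chance difference in baseline Mini-BESTest carries into that comparison in proportion to the baseline–post correlation, and a non-significant baseline test could be read as reassurance that it does not. The unadjusted tests also leave unused the precision that the baseline score offers in a small trial.

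**Working it through.** **Inputs from the protocol article.** 28 per arm randomised and 25 per arm after attrition; d = 0.71; alpha 0.05, two-sided. Two-sidedness is stated for the sample size and assumed for the baseline tests.

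**Assumptions, not in the document.** Baseline–post correlation ρ of 0.5, 0.7 and 0.8; an illustrative observed baseline imbalance of 0.5 SD, which is where the article's own effect-size bands begin to call a difference medium; equal SDs at both visits.

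**1. The plan's own figure.** For d = 0.71, two-sided 0.05 and 80% power, the two-sample t calculation gives 32.13, so 33 per arm (32 by normal approximation). The stated 25 per arm matches a one-sided normal calculation. Two-sided power at 25 per arm is 69%. The step from 50 to 56 for attrition reproduces. The sample-size discrepancy is a separate matter; only the 69% is used below.

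**2. What the baseline t-test lets through.** Baseline tests use everyone randomised, so n = 28 per arm.

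- Standard error in SD units: √(2/28) = 0.267.
- Smallest observed difference reaching p < 0.05: t(0.975, 54 df) × 0.267 = 2.005 × 0.267 = 0.54 SD.
- Observed 0.5 SD: t = 0.5/0.267 = 1.871, so p = 0.067.

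**3. How often this happens.** Under randomisation, an observed difference of at least 0.5 SD in a given continuous variable occurs in about 6.7% of trials, and 5% are flagged. So 6.7% − 5% = 1.7% have an imbalance that large which still passes.

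**4. Effect on the unadjusted post-intervention test.** Take no treatment effect, no attrition and an observed baseline difference of 0.5 SD. The post-intervention z statistic then has mean ρ × 0.5/0.267 and SD √(1 − ρ²).

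| ρ | Shift in post difference (ρ × 0.5) | Mean of z | SD of z | P(\|z\| > 1.96) |
|---|---|---|---|---|
| 0.5 | 0.25 SD | 0.935 | 0.866 | 12% |
| 0.7 | 0.35 SD | 1.310 | 0.714 | 18% |
| 0.8 | 0.40 SD | 1.497 | 0.600 | 22% |

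For ρ = 0.5, (1.96 − 0.935)/0.866 = 1.18, an upper tail of 0.118; the lower tail adds less than 0.001. The shifts are 0.25/0.71 = 35% to 0.40/0.71 = 56% of the planned effect. These rates are conditional on that imbalance. Averaged over all randomisations the test keeps its 5%.

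**5. What adjustment gains.** Adjusting for baseline reduces the residual SD by √(1 − ρ²). At 25 per arm the noncentrality is 0.71 × √(25/2)/√(1 − ρ²) = 2.510/√(1 − ρ²).

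| Analysis | Noncentrality | Two-sided power |
|---|---|---|
| Unadjusted (48 df) | 2.510 | 69% |
| Adjusted, ρ = 0.5 (47 df) | 2.899 | 81% |
| Adjusted, ρ = 0.7 | 3.515 | 93% |
| Adjusted, ρ = 0.8 | 4.184 | 98% |

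**The case against.** The strongest reply is that little depends on these tests. The practice is common, the baseline table is also descriptive, so readers can see any imbalance, and no stated outcome analysis is conditional on a baseline p-value. The mixed model comes first among the outcome analyses and has baseline as one of its time points, so its group-by-time interaction works on change from baseline.

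Much of this stands, and it limits the point. The mixed model does give partial protection. It is not complete: when baseline is simply one of the responses, a contrast of changes over-corrects a 0.5 SD imbalance by (1 − ρ) × 0.5, that is 0.25 to 0.10 SD for ρ of 0.5 to 0.8. The visit-wise tests have no such protection. Under non-normality the named alternatives are within-group tests plus Mann–Whitney, which leave no between-group comparison that refers to baseline.

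A reader might infer several stronger things that the document does not support.

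- *The tests miss a 0.5 SD imbalance more than half the time.* Power for a true 0.5 SD difference at 28 per arm is 45%, so 55% would be missed. But randomisation rules out a true difference between the populations from which the arms come. The relevant figure is the 1.7% of trials per variable in step 3.
- *The trial's type I error is inflated.* It is 5% overall; the 12–22% applies only given the stated imbalance.
- *Non-significant arms will be declared comparable.* The article states the tests' purpose but not this decision rule. They could be so described.
- *Randomisation is unrestricted.* The article gives 1:1 allocation by software and neither states nor excludes blocking or stratification, a detail that a condensed article may leave to the full protocol.

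**Conclusion.** The point holds in limited form. Baseline significance tests cannot serve the purpose that the plan gives them: at 28 per arm they pass any observed difference up to about 0.54 SD. The visit-wise between-group tests, which match the contrast behind the sample size, are unadjusted. With an observed 0.5 SD imbalance they would reject a true null in about 12–22% of trials.

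That range rests on assumed correlations of 0.5–0.8, a chosen imbalance and a normal approximation. Putting the t critical value 2.005 in place of 1.96 gives about 11%, 17% and 20%; for ρ = 0.5, (2.005 − 0.935)/0.866 = 1.235, a tail of 0.108. An unflagged imbalance of that size is uncommon, and the randomised comparison remains valid.

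The main reason to act is therefore efficiency. Removing the baseline p-values alone changes little. Routine baseline adjustment removes the dependence on chance imbalance in that score and raises power at 25 per arm from about 69% to about 81–98%. The power figures assume that d = 0.71 is standardised by the unadjusted post-intervention SD and that baseline and outcome are linearly related.

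**What to change.** In the Statistical analysis section:

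1. Delete the baseline significance tests and the clause that gives comparability as their purpose. Report baseline variables by arm descriptively, with standardised differences, and draw no conclusion about balance from p-values.
2. Replace the unadjusted visit-wise t and Mann–Whitney comparisons with baseline-adjusted between-group contrasts. Use either ANCOVA at each post-baseline visit, or the mixed model with baseline Mini-BESTest as a covariate and the two post-baseline visits as responses.
3. State that the adjustment is made whatever imbalance is observed.

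Wording such as this would do:

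> Baseline characteristics will be described by arm with standardised differences and will not be tested. The arms will be compared on Mini-BESTest after the intervention and at follow-up by contrasts adjusted for baseline Mini-BESTest, irrespective of any observed imbalance.

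The cost is a change of wording, one model term and the loss of the p-value column in the baseline table. Baseline assessments precede randomisation, so the covariate is already collected. The Data management section places the analysis after data collection is complete, so the change can be made and dated beforehand.

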### Allocation and blinding

Recruited patients will be randomly assigned to one of the two groups after the baseline evaluations. The sequence will be randomized, with a 1:1 allocation using randomization software (www.randomizer.org) between the experimental and the control group. Each participant will receive an identification code to ensure anonymity. Randomization will be conducted by an independent researcher who is not involved in the treatment or assessment. Outcome assessments will be performed by an evaluator blinded to group assignment, and the research team delivering the intervention will be excluded from all assessment activities to ensure a single-blind design.

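### Bonferroni for the post hoc comparisons is valid, but Holm gives the same familywise error control and never rejects less: a cheap, optional gain in power

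*Protocol article*

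**What the plan says.** All of this is in the protocol article.

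- **Statistical analysis, parametric route.** Linear mixed-effects models examine group-by-time interactions over three visits. Then: "Significant main or interaction effects will be further explored through Bonferroni-adjusted post hoc comparisons".
- **Statistical analysis, non-parametric route.** Within-group change is tested by Friedman and then by pairwise Wilcoxon tests. The section adds: "Bonferroni correction will be applied to control for multiple testing and Type I error".
- **Statistical analysis, level.** "The significance level will be 0.05 for all statistical analyses".
- **Statistical analysis, between-group tests.** A separate paragraph compares the groups at each visit by t-test or Mann-Whitney. It states no condition for running these tests and names no correction.
- **Sample size calculation.** The trial is sized "specifically on the expected difference between groups at the post-intervention time point", with 25 per group before attrition.

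**The concern.** The stated purpose of Bonferroni here is to control type I error across several comparisons. Holm does this equally well and is uniformly at least as powerful. In a trial with 25 evaluable participants per arm, choosing the weaker of two equally protective methods gives up some power. The loss falls mainly on the smaller effects, such as whether a gain is still present at 3 months. What is at stake is a few percentage points of power in individual post hoc comparisons. The validity of the trial's conclusions is not in question.

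**Working it through.** **1. Inputs.** From the protocol article: two-sided alpha 0.05, three visits, 25 per group, d = 0.71 between groups at post-intervention. Not given, so assumed: visit correlation (0.5, 0.7, 0.8), within-arm gains (0.5 SD at post, 0.35 SD at 3 months), and the between-group effect at 3 months (0.71 or 0.35).

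**2. The plan's own figure.** The article gives no power for post hoc comparisons, so only the group size can be checked. For two-sided 0.05 and 80% power, n per group = 2(1.960 + 0.842)²/0.71² = 31.1, so 32 (33 with the exact t). The one-sided formula gives 2(1.645 + 0.842)²/0.71² = 24.5, so 25. The stated 25 per group therefore fits a one-sided test, and its two-sided power at d = 0.71 is about 0.69. That is a separate matter; 25 is used below because it is the planned number.

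**3. The two rules, for k comparisons.**
- Bonferroni: reject every comparison with p ≤ 0.05/k. For k = 3 the limit is 0.0167.
- Holm: order the p-values and compare them with 0.05/k, 0.05/(k−1), …, 0.05, stopping at the first failure. For k = 3 the limits are 0.0167, 0.025 and 0.05.

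Every Holm limit is at least 0.05/k, so Holm rejects all that Bonferroni rejects. If m of the k nulls are true, the first true null that Holm reaches meets a limit of at most 0.05/m. Familywise error is therefore at most m × 0.05/m = 0.05. The first step is the Bonferroni step, so the chance of at least one rejection is the same.

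Made-up example: for p = 0.010, 0.020 and 0.040, Bonferroni rejects one comparison (0.020 > 0.0167). Holm rejects all three (0.020 ≤ 0.025 and 0.040 ≤ 0.05).

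**4. Within one arm, baseline versus 3 months.** Simulation of 40,000 arms with normal data, n = 25, the Friedman test at 0.05 as a first step, then three Wilcoxon pairs:

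| Visit correlation | Bonferroni | Holm | Gain (points) | Any rejection, both methods |
|---|---|---|---|---|
| 0.5 | 0.186 | 0.213 | 2.7 | 0.410 |
| 0.7 | 0.347 | 0.399 | 5.2 | 0.654 |
| 0.8 | 0.538 | 0.606 | 6.8 | 0.843 |

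The simulation standard error is at most √(0.25/40,000) = 0.0025. A smaller simulation of 3,000 arms gave 0.19 to 0.21, 0.35 to 0.39 and 0.55 to 0.62, which agrees within its error. Without the Friedman first step the gains are similar: 0.215 to 0.245, 0.373 to 0.430 and 0.554 to 0.627.

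**5. Between arms, if the visits are corrected together** (25 per group, t-tests, no first-step test, correlation 0.5 to 0.8):

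| Effect at post / 3 months | Family | Post: Bonferroni to Holm | 3 months: Bonferroni to Holm |
|---|---|---|---|
| 0.71 / 0.71 | 2 visits | about 0.58 to 0.63–0.64 | about 0.58 to 0.63–0.64 |
| 0.71 / 0.71 | 3 visits | 0.51–0.52 to 0.54–0.55 | 0.51–0.52 to 0.54–0.55 |
| 0.71 / 0.35 | 2 visits | about 0.58 to 0.58–0.59 | about 0.15 to 0.21–0.22 |
| 0.71 / 0.35 | 3 visits | 0.51–0.52 to 0.52 | about 0.12 to 0.14–0.15 |

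The gains run from about 0 to 7 points. If the contrasts are examined only after a significant interaction (three visits), post-intervention power goes from 0.40/0.49/0.51 to 0.43/0.52/0.54 at correlation 0.5/0.7/0.8 with d = 0.71 at both visits. It is almost unchanged (0.377/0.460/0.501 to 0.380/0.462/0.502) when the 3-month effect is 0.35.

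**6. Error control.** With all nulls true (three visit pairs, n = 50, correlation 0.7), familywise error is 0.044 for Bonferroni and 0.044 for Holm. With equal gains of 0.6 SD at both later visits (n = 25, correlation 0.7), the one true-null pair is rejected in 1.6% with Bonferroni and 4.0% with Holm. Both are below 5%.

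**The case against.** The strongest reply is that nothing here is wrong. Post hoc tests after an overall test, adjusted by Bonferroni, are common, valid and conservative, and they achieve the purpose the article states. The choice of multiplicity method is partly taste. Bonferroni also gives fewer false positives when some effects are real (1.6% against 4.0% above) and has simple matching intervals. The gains shown are mostly in within-arm change, which does not answer whether immersive virtual reality beats usual therapy. All of that stands, and it limits the point to an optional improvement.

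A reader might go further and infer a double penalty: an overall test as a gate, then Bonferroni as a redundant second correction, since with three visits the gate alone already protects the pairs. The documents do not support this as a criticism of the main analysis, for three reasons.

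- The three-visit argument holds for three means within one group. The main model has two groups and three visits. After a significant interaction the family can include visit pairs in each arm and between-arm contrasts, and the gate alone need not control error there.
- A significance condition is written only for the mixed-model route. For Friedman it is at most implied by the order of the tests.
- Replacing Bonferroni by Holm leaves any gate in place, so the change would not answer that complaint.

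Nor can one infer that the sizing comparison loses power through Bonferroni. The between-group tests at each visit have their own paragraph, with no gate and no named correction.

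**Conclusion.** Holm dominates Bonferroni for the planned post hoc comparisons. It has the same familywise guarantee, loses no rejection, and adds about 3 to 7 points for within-arm baseline versus 3 months and about 0 to 7 points for between-arm contrasts corrected together. The dominance needs no assumption. The sizes rest on 25 per arm, normal data, visit correlations of 0.5 to 0.8 and the assumed effects; the article gives neither the correlation nor the within-arm gains. The gain is in individual comparisons beyond the first, because the probability of at least one rejection is unchanged. The plan as written is valid. This is a cheap improvement at the lowest severity, not an error or a contradiction.

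**What to change.** In the Statistical analysis section, replace Bonferroni by Holm in both sentences that name it, applied to the same family of comparisons that Bonferroni would have covered. Report the unadjusted 95% confidence interval for each comparison beside its Holm-adjusted p-value. For ordered p-values this is the running maximum of (k − j + 1) × p(j), capped at 1. Record the change before the analysis starts; the article places analysis after recruitment and data collection are complete.

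The cost is one word in two places and a short calculation that may have to be done outside the software menus. Holm has no simple matching simultaneous intervals, which is why the unadjusted ones are suggested and should be labelled as such. If the investigators prefer simultaneous intervals, keeping Bonferroni is defensible.

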### Outcome measures

#### Primary outcome.

**Balance**. Balance performance will be assessed using the Mini-Balance Evaluation Systems Test (Mini-BESTest). This tool evaluates both static and dynamic balance impairments and identifies the risk of falls. It includes 14 items grouped into 4 domains: anticipatory postural adjustments, reactive postural control, sensory orientation, and dynamic gait. Each item will be evaluated on a 3-point ordinal scale ranging from 0 to 2, where 0 denotes minimal functional performance and 2 denotes optimal function. The total score can reach a maximum of 28 points, representing the absence of risk of falls [37]. The Mini-BESTest has demonstrated excellent test-retest reliability in individuals with PD [38,39].

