## Discussion

This randomized controlled trial protocol has been designed to analyze the effects of an IVR physical therapy program on balance improvement in individuals with PD. The primary objective of this study will determine whether the IVR intervention produces improvements in both static and dynamic balance in people with PD. In addition, this protocol includes several secondary variables that may indicate broader functional improvements, such as gait speed, functional mobility, overall lower limb strength, functional mobility, and quality of life. Adverse effects related to IVR exposure, participant satisfaction, and adherence will also be essential for evaluating the acceptability of the intervention.

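### A normality test on the observed variables appears to replace the group-by-time model with within-arm tests, leaving per-visit Mann–Whitney U as the only comparison of IVR with control

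*Protocol article*

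**What the plan says.** All the analysis rules are in the Protocol article, Statistical analysis.

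- Longitudinal analysis: "linear mixed-effects models will be employed to analyze" the group-by-time interaction over three measurement points.
- Distribution check: the Shapiro–Wilk "test will assess the normality of continuous variables". Model residuals are not mentioned.
- When the check fails: "In cases where data deviate from normality, within-group changes will be analyzed using the Friedman test, followed by Wilcoxon signed-rank tests for pairwise comparisons". No counterpart of the interaction is named for this case.
- Comparison of arms: "Between-group differences at each time point will be examined using independent-samples t-tests" "for normally distributed data, or Mann–Whitney U tests for non-parametric data". This applies in both branches.

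Under Sample size calculation, "the hypothesis anticipates superior outcomes for the experimental IVR intervention compared to the control condition", and the trial is sized on the between-group difference after the intervention. The Discussion words the aim more loosely: "The primary objective of this study will determine whether the IVR intervention produces improvements in both static and dynamic balance in people with PD". The primary outcome is the Mini-BESTest, a sum of 14 items scored 0 to 2: "The total score can reach a maximum of 28 points".

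**The concern.** Three features combine.

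1. **The route depends on the outcome data.** Which analysis is run is settled by a significance test on the observed values. A mixed model needs roughly normal residuals, and the marginal distribution of a bounded or skewed score says little about those.
2. **The fallback answers a different question.** Friedman and Wilcoxon tests within an arm ask whether that arm changed. They contain no contrast between IVR and control, so the between-group comparison of change disappears.
3. **The control arm is active.** Both arms receive the same strength programme and a graded balance programme, so both may improve. Significance in one arm only is then an easy chance result, and it can be mistaken for superiority.

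At stake are the precision of the between-group answer and the risk that within-arm p-values fill the gap.

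**Working it through.** The plan gives no figure for how often the switch would occur. The only figures of its own used here are d = 0.71, two-sided 0.05 and 25 evaluable (28 randomised) per arm. Means, SDs, correlations, gains and dz are assumptions.

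**1. How often would the switch fire?** The text does not say how many rejections are needed or which sets of values are tested. Assume that any one rejection at 0.05 suffices. With exactly normal data and independent tests, three tests (arms pooled) give 1 − 0.95³ = 14% and six (arm by visit) give 1 − 0.95⁶ = 26%. Simulation with 28 per arm, three visits and correlation 0.7 gave:

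| Assumed data | 3 pooled tests | 6 arm-by-visit tests |
|---|---|---|
| Exactly normal | 14–15% | 25–26% |
| Integer score capped at 28, mean 19, SD 5 | 28–30% | 31–32% |
| Same, mean 21 | 80–81% | 63% |
| Lognormal, log SD 0.35 (a skewed timed test) | 96% | 94% |

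A second simulation (25 per arm, SD 5, both arms gaining 2 points, six tests) gave 36–37% at baseline mean 18 and over 99% at baseline mean 22. At baseline mean 18, adding a true IVR effect of 0.71 SD raised the rate to 86–88%, because the IVR arm moves towards the cap. Under these assumptions a real benefit makes the switch more likely.

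**2. What does the surviving between-group test cost?** Take 25 per arm, d = 0.71, two-sided 0.05, post-intervention.

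- Unadjusted t-test: noncentrality 0.71 × √(25/2) = 2.51, power 69%. This is below the stated 80%, which is a separate matter, but it is the right benchmark here.
- Mann–Whitney U: about 65–67% by simulation with uncapped normal scores.
- Baseline-adjusted contrast: effective d = 0.71/√(1 − ρ²). At ρ = 0.5 this is 0.82, noncentrality 2.90, power about 80%. At ρ = 0.7 it is 0.99, noncentrality 3.51, power about 92%.

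The gain comes from adjusting for baseline. If baseline is simply one of three outcome times and the interaction is read as a difference in change, effective d = 0.71/√(2(1 − ρ)). That is 0.71 at ρ = 0.5 (power 69%) and 0.92 at ρ = 0.7 (noncentrality 3.24, power 89%).

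**3. How misleading could within-arm results be?** Suppose both arms truly gain the same amount. Let p be the power of a within-arm paired test at 0.05/3 = 0.0167 (Bonferroni over three pairs) with 28 per arm. IVR alone is significant with probability p(1 − p):

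| dz | p | p(1 − p) |
|---|---|---|
| 0.2 | 0.08 | 8% |
| 0.4 | 0.35 | 23% |
| 0.5 | 0.54 | 25% |
| 0.6 | 0.73 | 20% |
| 0.7 | 0.87 | 12% |
| 0.8 | 0.95 | 5% |

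The p values use the paired t-test as a stand-in for Wilcoxon. The second simulation, with no IVR effect and Wilcoxon tests on capped scores, gave IVR-only significance in 18–25% of trials. Mann–Whitney U after the intervention rejected in about 5%.

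**The case against.** The strongest reply is that a test of IVR against control survives. Mann–Whitney U is kept at each visit, and the post-intervention visit is the contrast the trial was sized on. In simulation it holds its 5% error rate, with power close to the t-test's (62–66% against 62–68% on capped scores). The plan also promises between-group effect sizes, with r for non-parametric analyses. This stands. A reader might infer that under non-normality the plan cannot test superiority at all, and the text does not support that.

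Other points on this side also hold:

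- The text does not say outright that the mixed model is abandoned; that is the natural reading of the sentence placed straight after it. If both were run, nothing says which governs, so the same clarification is needed.
- Nowhere does the plan say it will claim superiority because one arm is significant and the other is not. The stated hypothesis is between-group, and the looser Discussion sentence is not an analysis rule.
- Lack of baseline adjustment is not created by the switch, since the per-visit t-tests share it. In a randomised trial it costs precision, not validity.
- A reader might infer that Friedman breaches intention-to-treat by discarding participants with a missed visit. The same section provides for carrying observations forward or multiple imputation, so this does not follow.
- Discordance in either direction, 2p(1 − p), would be 39–50% at dz 0.4–0.6. Only the IVR-favouring half could suggest a false benefit.

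None of this restores a comparison of change between arms in the non-normal branch, or removes the data-driven choice.

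**Conclusion.** The concern holds in a limited form. The plan lets a normality test on observed variables steer the analysis. As naturally read, it then loses the group-by-time test and keeps only per-visit, baseline-unadjusted Mann–Whitney tests alongside within-arm tests.

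The switch is plausible for a score capped at 28 and likely for skewed timed tests. The rate of about 15–25% under exact normality depends on the assumed any-rejection trigger, and the higher rates also on assumed means, SD and skew. Against a baseline-adjusted contrast, the fallback gives up roughly 13 to 27 percentage points of power (80 − 67 to 92 − 65) at 25 per arm, d = 0.71 and correlation 0.5–0.7. Against a plain difference in change, the loss is small at correlation 0.5.

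The 20–25% rate of IVR-only significance is the peak of a curve. It applies to dz 0.4–0.6, which the documents do not give, and it does harm only if within-arm results are allowed to carry the conclusion.

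**What to change.** Change the Statistical analysis section as follows.

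- State that the mixed model's between-group contrast is the analysis for every continuous outcome, whatever Shapiro–Wilk shows. To obtain the precision shown above, adjust that contrast for baseline, for example with baseline as a covariate.
- Check the model's residuals instead of testing the raw variables.
- Handle marked skew on that same contrast, for example by log transform for TUG and TUG-DT, or by bootstrap or robust confidence intervals.
- Report within-group change, and any Friedman or Wilcoxon results, as descriptive only, and say that no conclusion about IVR against control rests on them.
- Mann–Whitney U at each visit may stay as a supporting analysis.

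The cost is wording: no extra participants, visits or measurements, and the planned software covers mixed models and bootstrap. Data management defers analysis until data collection is complete, so the change should be made and dated before any outcome data are examined.
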